## Abstract

**Background:**

High-sensitivity cardiac troponin (hs-cTn) assays are the gold standard for the early diagnosis and risk stratification of acute myocardial infarction (AMI). PERFORM-TSIX (clinicaltrials.gov identifier: NCT06734117) is a prospective, international, observational, longitudinal cohort study to evaluate the clinical performance of the next-generation Elecsys® Troponin T hs Gen 6 assay; the study design is presented here.

**Objectives:**

The primary objective is to determine the sensitivity of the Troponin T hs Gen 6 assay for the detection of centrally adjudicated AMI diagnosis at 3 h post-emergency department (ED) presentation. Secondary objectives include evaluation of clinical performance at 0, 1-, 5-, and 6-h post-ED presentation and validation of thresholds for a 0/1-h algorithm to rule out AMI. Exploratory objectives include validation of thresholds for a 0/1-h algorithm to rule in AMI and a 0/2-h algorithm to rule in/out AMI and evaluation of prognostic performance at 30 and 180 days.

**Methods:**

PERFORM–TSIX enrolled 5631 participants across 50 sites from the USA, Europe, China, and Japan. Patients aged ≥ 20 years presenting to the ED with symptoms/signs of acute coronary syndrome were enrolled. All patients were required to have cTn measured as part of their routine care; AMI diagnosis was adjudicated by an independent clinical events committee in accordance with the Fourth Universal Definition of MI, blinded to the results of the Troponin T hs Gen 6 assay.

**Conclusion:**

PERFORM-TSIX will determine the clinical performance of the Troponin T hs Gen 6 assay for the diagnosis of AMI in a large, diverse global population.

**Graphical Abstract:**

**Figure Figa:**
[figure not shown]

**Supplementary Information:**

The online version contains supplementary material available at https://doi.org/10.1007/s00392-025-02842-x.

## Introduction

Chest discomfort and other symptoms suggestive of acute myocardial infarction (AMI) are common reasons for patients to present to the emergency department (ED) [1]. In addition to clinical assessment and an electrocardiogram (ECG), measurements of cardiac troponin (cTn) are integral to the risk stratification and early diagnosis of AMI [2–6]. Diagnosis of AMI requires the detection of acute myocardial injury, defined as a rise and/or fall in cTn with at least one value above the sex-specific 99th percentile upper reference limit (URL), combined with clinical evidence of myocardial ischemia [5].

Clinical outcomes are dependent on a rapid and accurate diagnosis of AMI to ensure prompt treatment and coronary revascularization, as well as efficient disposition from the ED [7]. cTn measured by a high-sensitivity (hs) assay is considered the gold standard for the early risk stratification and diagnosis of AMI and is recommended by international guidelines [8–11]. The International Federation of Clinical Chemistry (IFCC) designates a cTn assay as hs when cTn is measurable above the lower limit of detection in more than half of all males and females in a healthy reference population, and the assay achieves a coefficient of variation (CV) of < 10% at the sex-specific 99th percentile URL [12, 13]. The introduction of hs-cTn assays allowed for the development of several accelerated algorithms, such as the European Society of Cardiology (ESC) 0/− 1 and − 2 h (h) algorithms, to support timely clinical decisions [8, 9, 14–18].

The next-generation Elecsys® Troponin T hs Gen 6 assay (Roche Diagnostics, Rotkreuz, Switzerland) has been developed using electrochemiluminescence technology to allow for rapid, quantitative *in vitro* determination of cTnT in serum and plasma. This assay has previously demonstrated higher analytical sensitivity and accuracy, especially at lower cTnT concentrations than earlier assay generations, as well as improved interference tolerance, most notably with respect to hemolysis [19]. This aims to optimize the performance of the assay for standard-of-care applications. Here, we present the design of PERFORM-TSIX, a prospective, international, observational, multicenter, longitudinal cohort study that aims to evaluate the clinical performance of the new Troponin T hs Gen 6 assay. The study is being conducted across multiple global regions in a representative, diverse population of patients presenting to the ED with suspected acute coronary syndrome (ACS), which may lead to a diagnosis of AMI.

## Methods

### Study design and study population

The PERFORM-TSIX study (retrospectively registered at clinicaltrials.gov [NCT06734117, December 2024]) is a prospective, international, observational, multicenter, longitudinal cohort study that aimed to enroll 5600 patients with suspected ACS across 50 sites from the United States of America (USA), Europe, China, and Japan [20]. Details on study sites are shown in Fig. 1 and suppl. Table 1. Recruitment commenced in November 2021 and continued for 31.5 months. In total, 5631 participants were enrolled across the regions (US, *n* = 3281; Europe, *n* = 1394; China, *n* = 831; Japan, *n* = 125). The study population was an all-comers cohort consisting of adults aged ≥ 20 years who presented to the ED with symptoms or signs of possible ACS. All patients were required to have cTn or other cardiac markers (creatine-kinase-MB) measured as part of their routine care. Patients were eligible for inclusion if they demonstrated symptoms suggestive of ACS and/or myocardial ischemia: chest pain; pressure; or a burning sensation across the precordium and epigastrium; pain that radiates (to neck, shoulder, jaw, back, upper abdomen, or either arm); acute onset or worsening dyspnea, gastrointestinal symptoms (nausea, vomiting, or indigestion); lightheadedness or syncope; diaphoresis; generalized weakness or fatigue; or if patients were asymptomatic but AMI was suspected.

**Fig. 1 Fig1:**
[figure not shown]
Map of study sites by region

Patients who met the inclusion criteria provided written informed consent prior to enrollment. The study was conducted in accordance with Good Clinical Practice and the Declaration of Helsinki, and ethical approval was obtained at each site from the pertinent ethical review board. A steering committee with expertise in cardiovascular biomarkers and AMI governed the PERFORM–TSIX study, which is funded by F Hoffmann-La Roche.

### Objectives

Objectives and outcome measures are detailed in Table 1. The primary objective is to determine the clinical performance of the Troponin T hs Gen 6 assay for the diagnosis of AMI at 3 h post-ED presentation. Secondary objectives are to evaluate the clinical performance at additional time points (0, 1, 5, and 6 h) post-ED presentation and to validate thresholds for use in a 0/1-h algorithm to rule out AMI. Exploratory objectives are to validate thresholds for a 0/1-h algorithm to rule in AMI and a 0/2-h algorithm to rule in and rule out AMI and to evaluate the prognostic value of the Troponin T hs Gen 6 assay at 30 and 180 days.

**Table 1 Tab1:** Summary of objectives and outcome measures for the PERFORM–TSIX study

	Objective	Outcome measure
Primary endpoint	• To determine the clinical performance of the Troponin T hs Gen 6 assay for the diagnosis of AMI at 3 h post-ED presentation using the previously determined universal and sex-specific 99th percentile URLs	• Sensitivity of the Troponin T hs Gen 6 assay for a CEC-adjudicated diagnosis of AMI when measured 3 h post-ED presentation (defined as samples taken 121–240 min post-ED presentation) • Acceptance criterion: > 81% for the LCL for sensitivity
Secondary endpoints	• To determine the clinical performance of the Troponin T hs Gen 6 assay additional time points using the previously determined universal and sex-specific a 99th percentile URLs	• Sensitivity, specificity, NPV and PPV of the Troponin T hs Gen 6 assay at additional time points (0 h [samples taken 0 to 60 min post-ED presentation], 1 h [samples taken 61 to 120 min post-ED presentation], 5 h [samples taken 241 to 360 min post-ED presentation] and 6 h [samples taken > 360 min post-ED presentation])
	• To validate thresholds for use in a 0/1-h algorithm to rule out AMI using the Troponin T hs Gen 6 assay	• NPV of the Troponin T hs Gen 6 assay to rule out AMI using a 0/1-h algorithm (0 h [samples taken 0 to 60 min post-ED presentation]/1 h [samples taken 30 to 90 min post-ED presentation]) • Acceptance criterion: > 98% for the LCL for NPV
Exploratory endpoints	• To validate thresholds for a 0/1-h algorithm to rule in AMI in patients presenting to the ED using the Troponin T hs Gen 6 assay	• Sensitivity, specificity, PPV and NPV of the Troponin T hs Gen 6 assay to rule in AMI using a 0/1-h algorithm (0 h [samples taken 0 to 60 min post-ED presentation]/1 h [samples taken 30 to 90 min post-ED presentation])
	• To validate a 0/2-h algorithm to rule in and rule out AMI in patients presenting to the ED using the Troponin T hs Gen 6 assay	• Sensitivity, specificity, PPV and NPV of the Troponin T hs Gen 6 assay to rule in and rule out AMI using a 0/2-h algorithm (0 h [samples taken 0 to 60 min post-ED presentation]/2 h [samples taken 91 to 150 min post-ED presentation])
	• To evaluate the prognostic value of the Troponin T hs Gen 6 assay at 30 and 180 days	• Risk prediction for MACE at 30 and 180 days for the different algorithmic outcome categories (rule-out, observe, rule-in)

*AMI* acute myocardial infarction, *CEC* clinical events committee, *ED* emergency department, *LCL* lower confidence limit, *MACE* major adverse cardiovascular outcomes, *NPV* negative predictive value, *PPV* positive predictive value, *URL* upper reference limit

### Outcomes

The primary diagnostic outcome measure is the sensitivity of the Troponin T hs Gen 6 assay for a clinical events committee (CEC)–adjudicated diagnosis of AMI when measured 3 h post-ED presentation (defined as samples collected 121 to 240 min post-ED presentation). Patients are only eligible for inclusion in the evaluation of the primary diagnostic outcome if at least one blood sample was collected within the defined timeframe of 121 to 240 min post-ED presentation. If more than one sample was collected within the window, the sample closest to the middle of the window will be used. Acceptance criterion for the primary endpoint is 81% for the lower confidence limit (LCL) for sensitivity.

Secondary outcome measures for the clinical performance of the Troponin T hs Gen 6 assay at additional time points are sensitivity, specificity, negative predictive value (NPV), and positive predictive value (PPV); measures to validate the thresholds for a 0/1-h algorithm to rule out AMI include sensitivity, specificity, NPV, and PPV. Acceptance criterion for the 0/1-h algorithm to rule out AMI is 98% for the LCL for NPV.

Exploratory outcome measures to validate the thresholds for a 0/1-h algorithm to rule in AMI and a 0/2-h algorithm to rule in and rule out AMI include sensitivity, specificity, NPV, and PPV.

To evaluate the prognostic value of the Troponin T hs Gen 6 assay, risk prediction for major adverse cardiovascular events (MACE) at 30 and 180 days will be analyzed for the different algorithmic outcome categories (rule-out, observe, rule-in).

### Study procedures

#### Sample collection, storage, and measurement

Venous blood samples were collected in serum and lithium-heparin (LiHep) plasma tubes within 1 h, and ideally within 30 min, of presentation to the ED (defined as time point [T]0). T0 was defined as registration in the ED; if patients arrived by ambulance and registration was not performed, triage time or the earliest time stamp available in the electronic case report form (eCRF) was used. Further samples were collected at 1, 2, and 3 h (T1–3) and up to 6 h (T6) post-ED presentation; target and acceptable blood collection times are detailed in Fig. 2. All blood samples were processed into serum and plasma and centrifuged in accordance with the guidelines of the sample tube manufacturers. Samples were then frozen at − 20 °C or colder within 4 h of blood draw. All samples were visually inspected prior to the experimental run to ensure no clots, precipitates, foam, or droplets on the container wall were present.

**Fig. 2 Fig2:**
[figure not shown]
Schematic diagram of the PERFORM–TSIX study design. ^a^Please see suppl. Table 3 for details

In the USA, Europe, and Japan, cTn in serum and LiHep plasma samples collected at the study sites were measured at one of five core laboratories, using the Troponin T hs Gen 6 assay on the Cobas® e 801 analyzer. In China, serum and LiHep plasma samples were measured at collection sites using the Troponin T hs Gen 6 assay on the Cobas e 801 analyzer. Details on testing sites are shown in suppl. Table 2. All samples were also measured using the current assay generation, Elecsys Troponin T (US)/Elecsys Troponin T hs Biotin PU STAT (rest of world) on the Cobas e 801 analyzer.

In addition to measuring cTn, multiple pathophysiological markers were measured to gather further information on comorbidities and to detect possible analytical interferences. Across all regions, a blood sample was used to measure N-terminal pro B-type natriuretic peptide (NT-proBNP), creatinine, and serum indices (hemolysis, icterus, and lipemia). In the USA, Europe, and Japan, bilirubin and triglycerides were measured from blood samples taken at each time point (results for individual time points will be excluded if out of range), whereas in China, levels were only measured once and will be applied to all time points. Ranges for exclusion were serum hemolysis index > 1000 (> 100 when using Elecsys Troponin T hs Biotin PU STAT assay); bilirubin > 25 mg/dL; or triglycerides > 1500 mg/dL; all tested at the testing site. Additional serum and plasma were retained for future use in other ethically approved studies.

#### Data collection

Data were collected and recorded in eCRFs and included patient demographics, vital signs, medical history, medications, electrocardiography, additional cardiac investigations, other routine laboratory testing, length of hospital stay, discharge/admission decision, any in-hospital cardiac events, and the final clinical diagnosis as recorded by sites. The full list of parameters that were collected is shown in suppl. Table 3. For adverse event (AE) and serious adverse event (SAE) reporting, the investigator determined if any AE/SAE occurred, and all study-related SAEs/AEs were recorded in the eCRF. SAEs were reported within 3 days of knowledge of the event.

#### Adjudication of the diagnosis of AMI

The diagnosis of AMI (type 1, 2, 4b, 4c) was adjudicated by a central and independent CEC in accordance with the Fourth Universal Definition of MI [5], blinded to the results of the Troponin T hs Gen 6 assay. AMI was defined as a rise and/or fall in cTn with at least one value above the 99th percentile URL, combined with clinical evidence of myocardial ischemia [5]. Each case was reviewed independently by two clinicians blinded to each other’s determination. If the reviewers’ diagnoses were the same, the diagnosis was finalized; if the reviewers’ diagnoses differed, a third clinician reviewed the presentation to establish the final adjudicated diagnosis. Each adjudicator had access to de-identified clinical data, including a description of symptoms, time of symptom onset, all 12-lead ECGs from the ED, echocardiography, cardiac stress testing and imaging, results of the local site cTn (including manufacturer and assay used, time of blood draw, result value and cut-offs used locally) and/or other cardiac biomarker tests, specified laboratory tests, treatment and hospital admission and discharge information. Results of the centrally measured current clinically available Elecsys Troponin T hs assay, NT-proBNP measurement and 30-day follow-up were also provided to the adjudicators. Based on all available clinical information, diagnosis was adjudicated in line with the Fourth Universal Definition of MI and classified into the following categories: (1) AMI (non-ST-elevation myocardial infarction (NSTEMI), ST-segment elevation myocardial infarction (STEMI), ECG not available or interpretable); (2) unstable angina; (3) cardiovascular non-coronary artery disease; (4) non-cardiac disease or symptoms of unknown origin. The clinical performance of the universal 99th percentile URL of the Troponin T hs Gen 6 assay was analyzed based on adjudication using the universal (non-sex-specific) cut-off for the current assay generation (Elecsys Troponin T hs) and performance of sex-specific 99th percentile URLs derived for the Troponin T hs Gen 6 assay were analyzed based on adjudication using sex-specific cut-offs. This was the gold standard diagnosis used to determine the clinical performance of the Troponin T hs Gen 6 assay.

#### Patient follow-up and outcomes

Patient follow-ups were conducted at 30 (+7) and 180 (+7) days post-ED presentation and consisted of a thorough chart review followed by a phone interview. To enhance the completeness of follow-up, patient calls were attempted on at least three different occasions. If approved by ethics committees, sites could also send a letter to the patient, and a follow-up reminder card could be provided at the time of enrollment.

Subsequent hospitalization for any cause, MACE (MI (including type of MI for the 30-day follow-up), all-cause death (cardiac and non-cardiac) [21]) occurring following discharge, and lost to follow-up rates were recorded in the eCRF (suppl. Table 3) for 30- and 180-day outcomes. Risk stratification and prognostic value of the Troponin T hs Gen 6 assay will be evaluated. For the 30-day follow-up only, any diagnostic or therapeutic procedures that occurred since discharge and the date they were performed (including ECG, echocardiogram, cardiac computed tomography scan, cardiac magnetic resonance imaging (MRI), stress tests, invasive angiography, percutaneous transluminal coronary angioplasty (urgent/routine), and coronary artery bypass graft (urgent/routine)) were recorded in the eCRF (suppl. Table 3).

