### Statistical analysis

Baseline characteristics, including distributions of age, sex, ethnicity, and race, will be summarized as proportions, mean and standard deviation, or median and inter-quartile range as appropriate in the study population, with stratification according to whether the final adjudicated diagnosis was AMI.

The universal and sex-specific 99th percentile URLs derived from a separate reference range study (REF-TSIX) will be used to classify the Troponin T hs Gen 6 assay results, with values above indicative of a potential AMI [5]. Sensitivity, specificity, NPV, and PPV will be calculated using cTnT measurements taken at sample analysis times T0, T1, T3, T5, and T6 (Fig. 2), based on all evaluable samples available at each time point. Clinical performance measures will be reported with 95% confidence intervals (CIs) estimated using the Wilson score method [22]. The results will be shown for the total cohort as well as separately for females and males (determined by sex assigned at birth). A subpopulation excluding STEMI patients will also be analyzed.

Thresholds and delta change values for rapid algorithms (0/1 h and 0/2 h) to rule out and rule in AMI for evaluation in this study will be determined in a separate cohort, independent of this analysis. The results of the independent cohort analysis will be validated in this PERFORM-TSIX study cohort. Sensitivity, specificity, PPV, and NPV will be calculated with 95% CIs for the rule-out and rule-in criteria.

Risk prediction based on Troponin T hs Gen 6 strata and prognostic value for the classification of the algorithmic outcome categories (rule-out zone, observe zone, rule-in zone) will be analyzed with respect to short-term (30-day) and long-term (180-day) outcomes (MACE [MI (including type of MI for the 30-day follow-up), all-cause death (cardiac and non-cardiac) [21]). The Kaplan–Meier method will be used to perform time-to-event analysis to compare the survival probabilities for different TnT strata and algorithmic outcome categories (rule-out zone, observe zone, rule-in zone). To this end, hazard ratios calculated from the Cox regression model and cumulative event-free rates will be reported to quantify the difference in risk between groups.

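### The 30- and 180-day MACE are recorded from discharge, but follow-up is timed from ED presentation and the analysis section has no discharge limit; index-stay deaths may go uncounted

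*Protocol article*

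**What the plan says.** Four places in the protocol article bear on the prognostic endpoint.

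- **Timing of contacts** (Patient follow-up and outcomes): "Patient follow-ups were conducted at 30 (+7) and 180 (+7) days post-ED presentation".
- **Events recorded** (same section, next paragraph): for the 30- and 180-day outcomes, the MACE components are MI and "all-cause death (cardiac and non-cardiac) [21]) occurring following discharge, and lost to follow-up rates were recorded in the eCRF". Procedures at the 30-day contact are likewise those since discharge.
- **Index-stay data** (Data collection): the eCRF also holds "length of hospital stay, discharge/admission decision, any in-hospital cardiac events, and the final clinical diagnosis as recorded by sites".
- **Analysis** (Statistical analysis): troponin strata and the rule-out, observe and rule-in zones "will be analyzed with respect to short-term (30-day) and long-term (180-day) outcomes", with MACE again made up of MI and all-cause death. "The Kaplan–Meier method will be used to perform time-to-event analysis", and "hazard ratios calculated from the Cox regression model and cumulative event-free rates will be reported to quantify the difference in risk between groups". This section has no discharge restriction and names no time zero.

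Table 1, under Objectives, lists this among the exploratory endpoints: "Risk prediction for MACE at 30 and 180 days for the different algorithmic outcome categories (rule-out, observe, rule-in").

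**The concern.** The window is counted from arrival in the ED, but the events recorded for it begin at discharge. Read literally, a patient who dies during the index stay never has a countable event, and a survivor cannot have one before going home. If the Kaplan–Meier and Cox analyses start at ED presentation, the index stay is then event-free by construction. If they start at discharge, that problem goes away, but the contact at 30 days from presentation covers only 30 minus the length of stay in days after discharge, so the result is not a 30-day rate from either origin.

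At stake is the prognostic claim itself. Patients classed as rule-in or observe are presumably those who are admitted, stay longest and die early most often. Leaving out their in-hospital deaths makes their curves look better than they are and may shrink the separation between zones that this objective is meant to describe.

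**Working it through.** The article gives no event count, event rate, hazard ratio or power for this endpoint, so there is no figure to reproduce. The check first compares the sections and then tests the direction of the effect under assumed risks.

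**1. The sections side by side**

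| Item | Patient follow-up and outcomes | Statistical analysis | Data collection |
|---|---|---|---|
| Clock | from ED presentation (contacts) | not stated | – |
| Death counted | after discharge | all-cause, no limit | in-hospital cardiac events recorded |
| MI counted | after discharge | MI, no limit | in-hospital cardiac events recorded |
| Link from in-hospital events to MACE | none | none | none |

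In-hospital cardiac deaths should therefore be in the data under "any in-hospital cardiac events", but nothing says that they enter MACE. In-hospital non-cardiac death is not named in the article text, although MACE includes it. The safety route does not clearly fill that gap, because only study-related adverse events are said to be recorded.

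**2. Effect on event-free rates** (assumed risks)

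Let *h* be the risk of in-hospital death and *p* the 30-day risk of MACE after discharge among those discharged alive. The event-free rate from presentation is (1 − h)(1 − p). With index-stay deaths ignored it is 1 − p if those patients are dropped, or 1 − (1 − h)p if they are kept as event-free.

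Rule-in, p = 5%:
- h = 1%: true 0.99 × 0.95 = 94.05%; reported 95.0% if dropped, or 1 − 0.99 × 0.05 = 95.05% if kept.
- h = 3%: true 0.97 × 0.95 = 92.15%; reported 95.0% if dropped, or 1 − 0.97 × 0.05 = 95.15% if kept.

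The reported rate is too high whenever h > 0. This part does not depend on what happens in the other zones.

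**3. Effect on the hazard ratio** (assumed risks)

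Under proportional hazards, HR = ln(1 − risk in rule-in) / ln(1 − risk in rule-out). Take post-discharge 30-day MACE as 5% in rule-in and 0.5% in rule-out:

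HR (post-discharge only) = ln(0.95)/ln(0.995) = 0.05129/0.00501 = 10.2.

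With in-hospital death added, HR = [−ln(1 − h_in) − ln(0.95)] / [−ln(1 − h_out) − ln(0.995)], where h_in and h_out are the in-hospital risks in rule-in and rule-out:

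| h_out | h_in | HR with index-stay deaths | Leaving them out (HR 10.2) |
|---|---|---|---|
| 0% | 1% | 12.2 | understates |
| 0% | 3% | 16.3 | understates |
| 0.05% | 3% | 14.8 | understates |
| 0.1% | 1% | 10.2 | no material change |
| 0.5% | 3% | 8.2 | overstates |

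The rule is simple. Leaving out in-hospital deaths pulls the ratio toward 1 only if the in-hospital rule-in to rule-out ratio exceeds the post-discharge ratio. With equal ratios nothing changes. With a smaller in-hospital ratio, the post-discharge figure lies too far from 1.

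**The case against.** The best reply is that the follow-up section describes what the follow-up contact recorded and does not define the analysed endpoint. A form asking about events since discharge, next to a separate form for the index stay, is an ordinary division of data collection. The contacts began with a chart review, which should reveal a death in hospital. The full parameter list is in supplementary Table 3, which is not shown, and an article may leave time zero and the handling of index-stay events to the SAP. For MI, a post-discharge rule also has a purpose: it keeps the index infarction out of the outcome.

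Much of this stands. A reader might infer that MACE is captured only after discharge, that in-hospital deaths are definitely excluded, and that the hazard ratio is definitely biased toward 1. The documents support none of these. In-hospital cardiac events are in the eCRF, no sentence excludes in-hospital deaths from the analysis, the origin of the survival analyses is not given, and the sign depends on rates that are not given.

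What does not stand is the view that nothing needs settling. The discharge limit is written into the description of the events for the 30- and 180-day outcomes, and the analysis section uses the same components without it. That is a conflict in stated text, not a detail left out. The reason for excluding the index MI does not extend to all-cause death.

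**Conclusion.** The point holds as an inconsistency with a conditional consequence. If the post-discharge wording governs, index-stay deaths are not counted, and 30- and 180-day event-free rates from presentation are too high in any zone where such deaths occur. Attenuation of the rule-in versus rule-out hazard ratio is the likelier result, because early deaths should concentrate in rule-in, but no change or a shift away from 1 is also possible.

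The size cannot be derived from the article; every risk used in the working is an assumption. A reader might be tempted to quote a share of events lost. With 5% 30-day death and 2% new MI after discharge in rule-in, and 30–70% of deaths in hospital, counted MACE falls from 7.0% to 0.05 × 0.7 + 0.02 = 5.5%, or to 0.05 × 0.3 + 0.02 = 3.5%, a loss of 21% to 50%. That range only returns its inputs and should not be read as an estimate for this study.

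The endpoint is exploratory, with no acceptance criterion and no sample size of its own. The primary sensitivity criterion and the secondary NPV criterion are untouched.

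**What to change.** Reconcile the sections on data collection, patient follow-up and outcomes, and statistical analysis by stating that:

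1. time zero for the Kaplan–Meier and Cox analyses is ED presentation;
2. all-cause death counts from that point, including death during the index stay;
3. MI counts only when it is a new event distinct from the adjudicated index event, with in-hospital events already in the eCRF as a source;
4. an analysis with time zero at discharge, among patients discharged alive, is shown as secondary and labelled as such.

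The cost is wording in the SAP and possibly a data query for dates of in-hospital death, including non-cardiac death if supplementary Table 3 does not already cover it. No new patient contact or sample is needed.
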